| Sample size considerations Anti-diabetic analyses  Sample sizes as per “feasibility counts” section, see table 1(below) for detectable differences in ethnic difference effect sizes. Corresponding to objective i), the proportion prescribed an anti-diabetic at 1 year post-diagnosis (42%) is taken from Sinclair et al (22) (detectable differences calculated using stpower cox command in Stata). Corresponding to objective ii), proportions prescribed metformin as first-line (73%) and a sulphonylurea as second line treatment (87%) are taken from Wilkinson et al (8) (power twoproportions command). Corresponding to objectives iv) and v), mean monitoring rate (2.45 times per year [extrapolated], assuming a SD of 2) (power twomeans command) and probability of treatment intensification at 1 year (24%) are taken from Khunti et al (23) (stpower cox command).  **Table 1. Detectable ethnic differences in outcomes.**   \| **Outcome** \| **Exposure (ethnicity): N vs. N** \| **Detectable ethnic difference effect sizes at α=0.05, β=0.90** \| \| --- \| --- \| --- \| \| Time from diagnosis to first anti-diabetic prescription \| South Asians vs. Europeans:  10.5K vs. 120.4K \| HR: 1.03 \| \| African Caribbeans vs. Europeans:  4.6K vs. 120.4K \| HR: 1.03 \| \| % prescribed metformin first-line \| South Asians vs. Europeans:  10.5K vs. 120.4K \| Difference in proportions: 1.4% \| \| African Caribbeans vs. Europeans:  4.6K vs. 120.4K \| Difference in proportions: 2.1% \| \| % prescribed sulphonylurea second-line \| South Asians vs. Europeans:  3.0K vs. 34.4K \| Difference in proportions: 2.0% \| \| African Caribbeans vs. Europeans:  1.3K vs. 34.4K \| Difference in proportions: 2.9% \| \| Mean monitoring rate, measurements per person year at risk \| South Asians vs. Europeans:  10.5K vs. 120.4K \| Rate difference: 0.07 \| \| African Caribbeans vs. Europeans:  4.6K vs. 120.4K \| Rate difference: 0.10 \| \| Time from sub-optimal diabetes control to treatment intensification \| South Asians vs. Europeans:  10.5K vs. 120.4K \| HR: 1.04 \| \| African Caribbeans vs. Europeans:  4.6K vs. 120.4K \| HR: 1.04 \| \| Time to antihypertensive initiation \| South Asians vs. Europeans:  7.6K vs. 119.4K \| HR: 1.02 \| \| African Caribbeans vs. Europeans:  3.8K vs. 119.4K \| HR: 1.02 \| \| Proportions of eligible people at high recorded CVD risk receiving statins \| South Asians vs. Europeans:  3K vs. 49K \| HR: 1.15 \| \| African Caribbeans vs. Europeans:  2K vs. 49K \| HR: 1.18 \|   Antihypertensive analyses  Sample sizes as per “feasibility counts” section. Little prior data exists in this area, but we can assume a mean time to measurement of 1 month (with an assumed SD of 1 month), as per guidelines for re-measurement after intensification (24). This would give a detectable ethnic difference in time until first monitoring as 0.04 months for South Asians vs. Europeans (using the power twomeans command in Stata), and 0.06 months for African Caribbeans vs. Europeans. Data from Petersen et al (25) suggest that 21% of those eligible for treatment for hypertension in the UK remain untreated. Adding this proportion to the expected numbers commencing antihypertensives by ethnicity (see feasibility count section), we would expect 119.4K Europeans, 7.6K South Asians and 3.8K African Caribbeans to be eligible for time to antihypertensive initiation analyses.  Lipid-lowering medication analyses  Sample sizes as per “feasibility counts” section. Assuming a mean time to monitoring of 3 months (26) and an SD of 1 month, the detectable ethnic difference in time until first monitoring would be 0.04 months for South Asians vs. Europeans, and 0.06 months for African Caribbeans vs. Europeans (using the power twomeans command in Stata). Chidwick et al reported that 24% of the high risk population received statins (21), equating to detectable ethnic differences in proportions receiving statins of HRs 1.18 and 1.15.  All detectable differences fall below what is likely to be considered clinically significant. |
| L. Definition of the Study population All permanently-registered patients with research-standard data and incident type 2 diabetes Read codes from at least 1 year after 1^st^ January 2006 (start of follow-up; coinciding with when ethnicity was recorded for ≈80% of new registrations (17)) to 31^st^ December 2018 in the CPRD. The study will be restricted to incident cases to enable more precise measurement of treatment stage; people with prevalent type 2 diabetes Read codes prior to 2006 will be excluded.  Type 2 diabetes will be defined by a previously tested algorithm that uses Read codes, medication, blood test results and diabetes-specific process of care Read codes to adjudicate diabetes status (27) – see appendix. Specific exclusions will include: type 1 diabetes, gestational diabetes, non-specified diabetes diagnosed at ≤40 years in Europeans or ≤35 years in South Asians and African Caribbeans (reducing misclassified type 1 diabetes), and secondary diabetes (e.g. drug-induced).  In people without diabetes, those eligible for antihypertensive treatment will include people ≥40 years of age with incident: Read codes for hypertension, clinic BP of ≥160/100, ambulatory BP of ≥150/95 or clinic BP of ≥140/90 or ambulatory BP of ≥135/85 **plus either** 10 year CVD risk score exceeding 20% or 10% (for calendar years 2006-2013 and 2014-2019 respectively) **or** evidence of target organ disease (i.e. Read codes for left ventricular hypertrophy, chronic kidney disease, micro/ macroalbuminuria, or hypertensive retinopathy) (24). Those eligible for lipid-lowering medication will include people ≥40 years of age with an incident recording of CVD risk score ≥20% (if recorded between 2006 and 2013), or ≥10% (if recorded between 2014 and 2019), to account for guidelines changes (26)) during the study period. |
| N. Exposures, outcomes and covariates *Data sources are listed in square parentheses*  Exposures:  For all objectives, the exposure is either South Asian or African Caribbean ethnicity (defined as above), with European ethnicity as the baseline category. *[Primary care clinical records]*  Health Outcomes by study objective:   1. Proportion of those eligible for primary prevention who are prescribed a) antihypertensives and b) lipid-lowering medication *[Primary care clinical records, prescription drug files]* 2. Time to first anti-diabetic/ antihypertensive/ lipid-lowering medication prescription. *[Primary care clinical records, prescription drug files.]* 3. Choice of a) anti-diabetic (first- to third-line), b) antihypertensive and c) lipid-lowering medications, see appendix for code lists for each (derived from chapters of the British National Formulary). *[Prescription drug files.]* 4. Doses used for each a) anti-diabetic, b) antihypertensive and c) lipid-lowering medication. *[Prescription drug files.]* 5. Monitoring rate, stratified by the time since treatment initiation, e.g. the number of a) HbA1c, b) BP or c) lipid measures divided by the amount of person time, within strata of time since initiation (i.e. first year, second year since initiation etc). *[Prescription drug files, test records.]* 6. Time to treatment intensification after detection of sub-optimal risk factor control. *[Primary care clinical records, prescription drug files, test records.]* Sub-optimal control will be classified as follows:    1. Diabetes; HbA1c≥53mmol/mol (7.5%) (7)    2. Hypertension; blood pressure≥140/80 mmHg, or 130/80 mmHg in those with neuropathy/ nephropathy or retinopathy (24)    3. Lipids; <40% reduction in non-HDL cholesterol (25) 7. Influence of the following on associations between ethnicity and prescribing: smoking, BMI, deprivation, polypharmacy, multi-morbidity, drug adherence (for outcomes iv) and v)), patient engagement with healthcare, diabetes duration and HbA1c. *[Linked IMD data, primary care clinical records, prescription drug files, test records.]*   Covariates (all taken from last entry in medical notes prior to follow-up time commencing)  Age *[Primary care clinical records]*  Sex *[Primary care clinical records]*  Smoking status *[Primary care clinical records]*  BMI *[Primary care clinical records]*  Deprivation (using patient-level IMD scores, with sensitivity analyses using practice-level IMD scores) *[Primary care clinical records, linked deprivation data]*  Polypharmacy (number of medications) *[Prescription drug files]*  Multimorbidity (defined by presence or absence of the following key co-morbidities: coronary heart disease, cerebrovascular disease, heart failure, atrial fibrilliation, hypertension, chronic kidney disease, peripheral arterial disease, retinopathy, neuropathy, cancer [any], COPD/ asthma, severe mental illness) *[Primary care clinical records]*  Patient engagement/ access (using the number of consultations in the year preceding diabetes diagnosis as a proxy) *[Primary care clinical records]*  Patient adherence (using the proportion of days covered: PDC=days of medication supplied per x day period/ x (27)). This will be calculated separately for all medications issued over the follow-up time of interest, and then a mean PDC for all medications will be derived for each patient. Both measures are important as adherence may vary by drug. *[Prescription drug files]*  Disease parameters: baseline HbA1c/ blood pressure and number of years since diabetes diagnosis *[Primary care clinical records, test records.]* |
| O. Data/ Statistical Analysis For all parts of the study, the population will be people with and without new-onset type 2 diabetes active in CPRD from 2006 (see section K, above) and the exposure will be ethnicity (either South Asian vs. European [baseline] or African Caribbean vs. European [baseline], as detailed in section L, above). Covariates in base models will include age and sex, and further covariates will be considered individually, as outlined in section vi) below. Statistical analysis is further considered by objective:   1. **Outcome:** Proportion of those eligible for primary prevention who are prescribed a) antihypertensives and b) lipid-lowering medication   **Entry:** Date of incident a) hypertension Read code/ raised BP reading or b) elevated 10 year CVD risk score, at least 12 months after study start date of 1^st^ January 2005  **Exit:** First of; date of first antihypertensive/ lipid-lowering medication prescription (defined by the absence of a prescription for the medication in the previous 6 months’ records), end of study, leaving CPRD practice or death  **Analysis:** Proportions receiving antihypertensives/ statin will be compared by ethnicity, then logistic regression models will be used to adjust for confounding/ investigate potential mediators  **Example effect measure:** Odds ratio (OR) of receiving an antihypertensive/ lipid-lowering medication vs. not for each ethnic group of interest, stratified by time period since identification of hypertension/ elevated CVD risk   1. **Outcome**: time to initiation of first-line anti-diabetic/ antihypertensive/ statin, probability of receiving anti-diabetic/ antihypertensive/ statin at one year post-diagnosis/ identification of high CVD risk   **Entry**: date of type 2 diabetes diagnosis/ incident hypertension Read code or raised BP reading/ incident high 10 year CVD risk score recording  **Exit**: date of first anti-diabetic/ antihypertensive/ statin prescription (defined by the absence of a prescription for the medication in the previous 6 months’ records), or end of study/ leaving CPRD practice/ death  **Analysis**: summary statistics will be compared by ethnicity using Kaplan-Meier time-to-event analysis (cumulative failure probability in a given time frame by ethnicity, comparison of medians by log-rank test), Cox proportional hazards regression models will be used to adjust for confounding/ investigate potential mediators  **Example effect measure**: hazards ratio (HR) for anti-diabetic/ antihypertensive/ statin prescription   1. **Outcome:** proportions of patients prescribed medication from each anti-diabetic (stratified by first- to third-line treatment), antihypertensive and lipid-lowering class (defined by the absence of a prescription for the medication in the previous 6 months’ records)   **Sub-population:** a) all participants starting first- to third-line anti-diabetic treatment, b) all patients on antihypertensives, or c) all patients on lipid-lowering medication  **Analysis:** proportions receiving each drug will be compared by ethnicity, then logistic regression models will be used to adjust for confounding/ investigate potential mediators  **Example effect measures**: odds ratio (OR) of being prescribed metformin (=1) vs. non-metformin medication (=0) at first stage of treatment, OR of being prescribed sulphonylurea (=1) vs. non- sulphonylurea medication (=0) at second stage of treatment, OR of calcium-channel blocking antihypertensive prescription vs. non- calcium-channel blocking antihypertensive in those on antihypertensive treatment, OR of statin prescription vs. non-statin lipid-lowering medication prescription in those with >10% 10 year cardiovascular risk   1. **Outcome:** proportions of patients prescribed each dose of each anti-diabetic, antihypertensive and lipid-lowering medication, stratified by treatment stage (defined by the absence of a prescription for the medication in the previous 6 months’ records)   **Sub-population:** a) all participants on first- to third-line anti-diabetic treatment, b) all patients on antihypertensives, or c) all patients on lipid-lowering medication  **Analysis: :** proportions receiving each dose of each drug will be compared by ethnicity, then logistic regression models will be used to adjust for confounding/ investigate potential mediators  **Example effect measures**: OR of being prescribed maximum dose (2g daily) vs. sub-maximum dose of metformin, OR of being prescribed atorvastatin 10mg per day vs. higher doses (20mg, 40mg or 80mg)   1. **Outcome:** yearly monitoring rate post commencement of medication from each anti-diabetic (first- to third-line), antihypertensive and lipid-lowering class – i.e. number of times HbA1c/ blood pressure/ blood lipids measured per person-year of follow-up, stratified by year after commencement; may be multiple entry dates per person for different medications   **Entry:** first use of any medications of interest from 2006 onwards  **Exit:** first of; end of strata (e.g. 1 year after medication commencement), end of study/ leaving CPRD practice/ death  **Analysis:** summary statistics will be compared by ethnicity, Poisson regression modelling used to adjust for confounding/ investigate potential mediators  **Example effect measures**: yearly monitoring rate ratios (RRs)   1. **Outcome:** time to medication intensification (up-titration, addition or switching) after detection of sub-optimal control of diabetes, hypertension or blood lipids, or probability of intensification 1 year post-detection of sub-optimal control; may be multiple entry dates per person for different medications   **Entry:** date when sub-optimal risk factor control detected (see section M for how this is defined for each risk factor)  **Exit:** first of; date of anti-diabetic, antihypertensive or lipid-lowering treatment intensification, end of study/ leaving CPRD practice/ death  **Analysis:** summary statistics will be compared by ethnicity using Kaplan-Meier time-to-event analysis (cumulative failure probability in a given time frame by ethnicity, comparison by log-rank test), Cox proportional hazards regression models will be used to adjust for confounding/ investigate potential mediators  **Example effect measures**: cumulative failure probability for each ethnic group 1 year post detection of sub-optimal value, comparison of median survival times using the log-rank test by ethnicity, HRs of intensification stratified by year   1. **Outcome:** influence of deprivation, polypharmacy, multi-morbidity, drug adherence (iv) and v) only), patient engagement with healthcare, diabetes duration and HbA1c on any ethnic differences found in i) to v).   **Entry:** as above for i), iv) and v)  **Exit:** as above for i), iv) and v)  **Analysis:** as above for i) to v)  **Covariates:** smoking status, BMI, deprivation, polypharmacy, multi-morbidity, drug adherence, patient engagement with healthcare, diabetes duration and HbA1c  **Effect measures:** we will observe the degree of attenuation of the ethnic difference effect measure for each outcome when each covariate is inserted in turn to models, and thus evaluate the likelihood of confounding or mediation  Sub-group/ sensitivity analyses  See section O of original application  Plans for addressing misclassification and bias  See section O of original application  Multiple comparisons  See section O of original application |

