| Feasibility counts The primary analysis will be using data from CPRD alone (see section M for sensitivity analyses). Ethnicity recording for active patients is approximately 50% (17, 18). The ethnic breakdown is similar to that of the UK census 2011(20).  From 2000-2017, ≈280K patients initiated first-line and ≈80K second-line treatment for type 2 diabetes in CPRD (8). If 50% of these people had ethnicity codes present in their record, this would correspond to ≈140K starting first-line and ≈40K starting second line treatment. Using the 2011 census to calculate proportions, this would equate to ≈120.4K Europeans, ≈10.5K South Asians and ≈4.6K African Caribbeans initiating first-line treatment and 34.4K, 3.0K and 1.3K respectively starting second-line treatment. These are conservative estimates given the over-representation of ethnic minorities in the diabetic population.  Approximately 77% of the people with diabetes initiating first-line treatments are likely to be on antihypertensives (19), giving numbers for antihypertensive analyses of ≈92.7K Europeans, ≈8.1K South Asians, ≈3.5K African Caribbeans. Previous work in CPRD shows that ≈64% of people with type 2 diabetes receive statins (19), which will yield numbers for the lipid-lowering medication analyses of ≈77.1K Europeans, ≈6.7K South Asians and ≈2.9K African Caribbeans.  For people without diabetes, we expect approximately 219K people to initiate antihypertensive treatment over a similar study period to our own (20), equating to at least 94K Europeans, 6K South Asians and 3K African Caribbeans, once multipliers for ethnicity recording and the 2011 Census ethnicity breakdown are applied. From Chidwick et al (21), 113,035 people over 40 without a prior history of CVD had a high CVD risk score recorded between 2005-2013. Assuming 50% of these people had ethnicity recorded, and proportions by ethnicity are as per the 2011 census, this equates to approximately 49K Europeans, 3K South Asians and 2K African Caribbeans. |

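### The Table 1 rows for time to first anti-diabetic prescription pair a count of treatment initiators with a one-year event share that applies to all newly diagnosed people

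*Supplement*

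**What the plan says.** All references are to the amendment of 9 December 2019.

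- **Feasibility counts.** The starting figure is "280K patients initiated first-line and ≈80K second-line treatment for type 2 diabetes in CPRD". Halving it for ethnicity recording and applying census shares gives "120.4K Europeans, ≈10.5K South Asians and ≈4.6K African Caribbeans initiating first-line treatment".
- **Sample size considerations, anti-diabetic analyses.** These counts are carried over unchanged: "Sample sizes as per “feasibility counts” section, see table 1(below) for detectable differences in ethnic difference effect sizes". The event input for time to initiation is "the proportion prescribed an anti-diabetic at 1 year post-diagnosis (42"%), used with Stata's Cox power command.
- **Table 1.** Time from diagnosis to first anti-diabetic prescription is sized on "10.5K vs. 120.4K" and "4.6K vs. 120.4K", with a detectable HR of 1.03 in both rows at α=0.05 and 90% power (printed as β=0.90).
- **Sample size considerations, antihypertensive analyses.** Here the number starting treatment is raised to the number eligible, using 21% untreated: "Adding this proportion to the expected numbers commencing antihypertensives by ethnicity".
- **Sections L and O (objective 2).** The cohort is incident type 2 diabetes, 2006 at the earliest to the end of 2018. Follow-up runs from diagnosis to "date of first anti-diabetic/ antihypertensive/ statin prescription", end of study, leaving the practice or death.

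**The concern.** The two inputs have different denominators. The 42% is a share of everyone newly diagnosed, whether or not they are ever treated. The group sizes contain only people who did start treatment. Someone diagnosed and never treated belongs to the risk set in section O but is missing from N. Conversely, if the counted initiators fall within the cohort, each of them contributes an event over the planned follow-up, not 42% of them.

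The parallel antihypertensive rows were put on an eligible-population basis and these were not, so the time-to-initiation rows of one table cannot be compared.

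What is at stake is the accuracy of two printed detectable effects. The mismatch also interacts with a second problem in the same rows, the ethnic split. Correcting only one of the two would give figures that are still off.

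**Working it through.** **Inputs.** N = 130.9K (10.5K + 120.4K; South Asian share a = 0.0802) and 125.0K (4.6K + 120.4K; African Caribbean share a = 0.0368). Event probability pE = 0.42. α = 0.05, taken as two-sided because the plan does not say. Power 90%.

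**Formula (Schoenfeld).** HR = exp[(1.960 + 1.282) / √(E·a(1−a))], where E = N·pE is the number of events.

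**Step 1: reproduce the printed 1.03 and 1.03.**

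- Actual shares, South Asian: E = 0.42 × 130,900 = 54,978; a(1−a) = 0.0738; HR = exp(3.2415/63.7) = 1.052.
- Actual shares, African Caribbean: E = 0.42 × 125,000 = 52,500; a(1−a) = 0.0354; HR = exp(3.2415/43.1) = 1.078.
- Equal split, a(1−a) = 0.25: 1.028 and 1.029. Both round to 1.03.

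With actual shares, 80% power gives 1.045/1.067, a one-sided test at 90% power gives 1.047/1.070, one-sided at 80% gives 1.040/1.059, and Freedman's formula gives 1.051/1.075. None matches both rows. The equal split also reproduces the anti-diabetic intensification rows (pE 0.24: 1.037/1.038, printed 1.04) and the antihypertensive initiation rows (pE 0.79: 1.021/1.021, printed 1.02). It is inferred from these matches; the plan does not state it. The statin rows do not follow it (an equal split would give 1.06 against the printed 1.15 and 1.18).

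**Step 2: isolate the denominator mismatch.** Keep the equal split and let events equal the initiator count, E = N. The HR falls from 1.028/1.029 to 1.018/1.018, that is, 1.02. On its own, the mismatch makes the printed HR too large.

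**Step 3: check the antihypertensive rows.** 94K/0.79 = 119.0K (printed 119.4K; the source figure is given as at least 94K), 6K/0.79 = 7.6K, 3K/0.79 = 3.8K. With pE 0.79, events are 0.79 × 127.0K = 100.3K and 0.79 × 123.2K = 97.3K, close to the initiator counts of 100K and 97K. In effect those rows use initiators as events.

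**Step 4: consistent inputs with the actual shares.**

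| Basis | South Asian | African Caribbean |
|---|---|---|
| As printed | 1.03 | 1.03 |
| Printed N, 42% events | 1.052 | 1.078 |
| Initiators as events (130.9K; 125.0K) | 1.034 | 1.050 |
| Two thirds of those events (illustrative) | 1.04 | 1.06 |
| One-year 42%, N divided by an assumed ever-treated share of 70–90% | 1.044–1.049 | 1.065–1.074 |

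The two-thirds row divides the log HR by √(2/3): 0.0330/0.816 = 0.040 and 0.0487/0.816 = 0.060. In the last row, E = 0.42·N/f. The documents give no ever-treated share f. Over its full possible range, 0.42 to 1, the HR runs from 1.034 to 1.052 and from 1.050 to 1.078.

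**Step 5: power at the printed HR of 1.03, actual shares.** Power = Φ(ln 1.03·√(E·a(1−a)) − 1.960). With 42% events: 47% (South Asian) and 25% (African Caribbean). With initiators as events: 83% and 50%.

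**The case against.** The strongest defence is that the pairing is a cautious approximation. Everyone who starts treatment has been diagnosed, so the initiator count can serve as a lower bound on the diagnosed cohort. A one-year share also fits a planned outcome, since section O, objective 2, lists the probability of receiving treatment at one year alongside time to initiation. The two inputs would even be compatible if the calculation were confined to year 1 and everyone diagnosed eventually started treatment.

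Much of this stands. The mismatch is conservative, and it would be too strong to say that the inputs cannot both hold. But the plan states neither of those conditions, does not call the figure a lower bound or a year-1 figure, and sets no one-year cut for the Cox model.

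A reader might infer that the mismatch is why the printed HRs are too small. The documents do not support that: Step 2 shows that it pushes the other way. The fall in power to 47% and 25% arises from replacing the equal split with the actual group sizes.

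A further objection is that initiators cannot simply be counted as events, because the 280K covers 2000–2017 while the cohort is incident cases from 2006 to 2018. That also stands. The count includes people who started treatment before the cohort opened, so 1.034 and 1.050 depend on an assumption.

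**Conclusion.** The concern holds as an inconsistency of inputs. The two rows combine treatment initiators with a one-year share of newly diagnosed people, and the resulting 55.0K and 52.5K events do not describe the planned analysis. The understated HRs come from the inferred equal ethnic split, which is a separate error in the same rows.

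With both corrected, the South Asian figure may stay near 1.03. The African Caribbean figure of 1.03 fails on every basis that uses the actual group sizes and becomes about 1.05 or higher. Correcting only the split would print 1.05 and 1.08, which overstates the detectable effect if all counted initiators are in the cohort.

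A reader might go on to infer that the study is too small for this outcome. That does not follow: the largest value found is 1.08, still a small effect. The conclusion assumes a two-sided test, 90% power and a Schoenfeld-type calculation; the exact values depend on how many counted initiators fall in the cohort, or on the assumed ever-treated share.

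**What to change.** Put the two rows on one stated basis, with the actual group sizes. Either route works.

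- **Initiators as events**, as the antihypertensive rows in effect do. Print HR about 1.03 (South Asian) and 1.05 (African Caribbean). Restrict the count to initiators in the cohort window, or state the assumption that all of them fall in it; keeping two thirds of the events, for example, gives about 1.04 and 1.06.
- **Year-1 basis.** Keep 42%, divide the initiator counts by a stated, assumed ever-treated share, and label the result as the detectable HR for year 1. Shares of 70–90% give about 1.044–1.049 and 1.065–1.074. This would still not match the antihypertensive rows, so the difference in basis should be noted under the table.

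The first route keeps the time-to-initiation rows comparable if the antihypertensive rows are also recalculated with their actual group sizes. The cost is two table rows and a sentence; data, cohort and analysis are unaffected.

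### Six hazard ratios in Table 1 match a calculation with equal-sized groups, not the listed group sizes, so the 90% power claimed for them does not hold on the plan's own inputs

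*Supplement*

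**What the plan says.** The relevant text is in the amendment of 9 December 2019, under Sample size considerations and Feasibility counts.

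- Table 1 is headed "Detectable ethnic difference effect sizes at α=0.05, β=0.90". Each row lists its own group sizes.
- The two anti-diabetic time-to-event outcomes use 10.5K South Asians and 4.6K African Caribbeans, each against 120.4K Europeans. The text names the Stata Cox command for both: "detectable differences calculated using stpower cox command in Stata" for initiation, and the same command again for intensification. The event proportions are 42% prescribed at 1 year and 24% intensified at 1 year.
- Time to antihypertensive initiation uses 7.6K and 3.8K against 119.4K. No command is named. The nearest event proportion comes from the statement that "21% of those eligible for treatment for hypertension in the UK remain untreated", which implies 79% treated.
- The printed hazard ratios (South Asian/African Caribbean) are 1.03/1.03, 1.04/1.04 and 1.02/1.02.
- The statin row concerns a proportion but is printed as hazard ratios of 1.15 and 1.18. The text describes it as "equating to detectable ethnic differences in proportions receiving statins of HRs 1.18 and 1.15".
- The section closes: "All detectable differences fall below what is likely to be considered clinically significant".

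Neither the proportion exposed nor the SD of the exposure indicator is given for the Cox rows, and equal allocation is not mentioned.

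**The concern.** At fixed power, halving the smaller group against the same comparator must raise the detectable effect noticeably. It does so in every other row of Table 1: the monitoring-rate difference goes from 0.07 to 0.10, the metformin difference from 1.4% to 2.1%, and the sulphonylurea difference from 2.0% to 2.9%. In three Cox outcomes it does not move at all.

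For a binary exposure, the information in a Cox model is the number of events times p(1−p), where p is the exposed share. That product is 0.25 for a 50:50 split but only about 0.03 to 0.07 for the shares listed here. If the Cox rows were run as 50:50, the table mixes two allocation assumptions under one 90% heading and overstates the precision of three time-to-event comparisons. The overstatement is largest for African Caribbeans, the smallest group. The closing statement on clinical significance also rests partly on those rows.

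**Working it through.** **Inputs.** Group sizes and event proportions are those listed above. Alpha is taken as two-sided 5%, because the plan does not state the sidedness. The β=0.90 in the table heading is read as power 0.90. Then z(0.975)+z(0.90) = 1.960+1.282 = 3.2415, with square 10.507.

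**Formula (Schoenfeld).** ln HR = 3.2415 / √(D·p(1−p)), where D is total N times the event proportion and p is the exposed share. Power at a stated HR is Φ(ln HR·√(D·p(1−p)) − 1.960).

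**Step 1: reproduce the plan.** Set p(1−p) = 0.25. For initiation in South Asians, D = 130,900 × 0.42 = 54,978, so ln HR = 3.2415/√(54,978 × 0.25) = 0.0276 and HR = 1.028. All six rows follow in the same way and round to the printed figures (fourth column below).

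**Step 2: use the listed sizes.** For the same row, p = 10.5/130.9 = 0.0802 and p(1−p) = 0.0738. Then ln HR = 3.2415/√(54,978 × 0.0738) = 0.0509 and HR = 1.052.

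| Row | D | p | HR at 50:50 | Printed | HR at listed sizes | Power at printed HR |
|---|---|---|---|---|---|---|
| Initiation, South Asian | 54,978 | 0.0802 | 1.028 | 1.03 | 1.052 | 47% |
| Initiation, African Caribbean | 52,500 | 0.0368 | 1.029 | 1.03 | 1.078 | 25% |
| Intensification, South Asian | 31,416 | 0.0802 | 1.037 | 1.04 | 1.070 | 47% |
| Intensification, African Caribbean | 30,000 | 0.0368 | 1.038 | 1.04 | 1.10 | 25% |
| Antihypertensive, South Asian | 100,330 | 0.0598 | 1.021 | 1.02 | 1.044 | 32% |
| Antihypertensive, African Caribbean | 97,328 | 0.0308 | 1.021 | 1.02 | 1.062 | 19% |

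The SD of the exposure indicator, √(p(1−p)), runs from about 0.17 to 0.27 in these rows. A 50:50 split gives 0.5.

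**Step 3: alternatives at the listed sizes.** One-sided alpha gives 1.047/1.070, 1.063/1.094 and 1.040/1.056. Power of 80% gives 1.045/1.067, 1.060/1.090 and 1.038/1.053. Freedman's formula with unequal allocation gives 1.051–1.053/1.075–1.081, 1.068–1.072/1.100–1.110 and 1.043–1.045/1.060–1.064. None of these recovers the printed set.

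**Step 4: robustness.** Moving the printed HRs by ±0.005 for rounding puts power anywhere from about 12% to 59%, depending on the row. If every patient had the event (D = N), power at the printed HRs is 83/50% for initiation, 97/74% for intensification and 39/22% for antihypertensive initiation. Five of the six still fall short of 90%.

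**Step 5: the other rows.** The monitoring rows (SD 2) give 3.2415 × 2 × √(1/10,500 + 1/120,400) = 0.066 and, with 4,600, 0.097, against the printed 0.07 and 0.10. The two-proportion rows, for increases from 73% and 87%, come to about 1.5/2.1 and 2.0/3.0 percentage points, against 1.4/2.1 and 2.0/2.9. These rows do use the listed sizes.

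**Step 6: the statin row.** A two-proportion calculation from 24%, with 3K and 2K against 49K, gives increases of 2.64 and 3.21 points.
- South Asian: (0.2664/0.7336)/(0.24/0.76) = 1.150.
- African Caribbean: (0.2721/0.7279)/(0.24/0.76) = 1.184.

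These are the printed 1.15 and 1.18, so the figures are odds ratios. The Cox values at the same sizes would be 1.13 and 1.16.

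**The case against.** **Impact.** The data are existing records, there is no recruitment target, and the corrected hazard ratios are still only about 1.04 to 1.10. The same table prints 1.15 and 1.18 and calls all detectable differences smaller than what would matter clinically. The documents set no threshold that the corrected values cross. This stands, and it limits the severity.

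**Event counts.** The quoted power depends on 1-year event proportions, whereas follow-up in section O runs to end of study, leaving the practice or death. The Feasibility counts are also of people who started treatment, so for initiation all of them had the event. Counting them that way gives detectable hazard ratios of 1.034/1.050 and power of 83/50% at 1.03. This also stands. The 19–47% range is one scenario, though it is the plan's own: the 42%, 24% and inferred 79% are what reproduce the printed values. It does not rescue the table, as Step 4 shows.

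**Equal allocation is inferred.** No section states it. The support is six matches out of six, identical pairs despite a twofold difference in minority group size, and no match from the alternatives tried.

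**Are the group sizes uniformly too favourable?** A reader might infer this, because the intensification row counts all initiators and not only those reaching the HbA1c threshold, and because the 280K count covers 2000–2017. The documents do not support so general a reading. For initiation, everyone diagnosed is at risk, which is more people than the initiators. The plan calls its minority counts conservative. The lower South Asian share in the non-diabetes counts (6/109.5 = 5.5% and 3/56.5 = 5.3%, against 10.5/140 = 7.5%) makes those rows less favourable. No document says how many people reach the threshold.

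**Would a null result be read as excluding differences of 2–4%?** The plan does not say so. Its multiple-comparisons text, carried into the amendment by reference, promises caution and attention to effect sizes over p values.

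**Conclusion.** The point holds for the six Cox rows: they match a 50:50 exposure split and not the sizes printed beside them. On the plan's own sizes and event proportions, at two-sided 5% and 90% power, the detectable hazard ratios are about 1.05/1.08, 1.07/1.10 and 1.04/1.06. The assumptions are the inferred 79% for antihypertensive initiation, the two-sided test, and the 1-year proportions as the event fraction. More events would narrow the gap, but only South Asian intensification could reach 90% at its printed value.

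The statin row does not share the fault. It uses the unequal sizes, and on the Cox scale its values would have about 95% power, so the defect there is the label.

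Two stronger conclusions are tempting and not supported. The study as a whole cannot be called underpowered, because the corrected effects are still small. Nor does the closing statement have to be withdrawn, since by the plan's own tolerance of 1.15 and 1.18 it can survive once it rests on correct figures. Severity is minor to moderate.

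**What to change.** 1. Recompute the six Cox rows with exposure SD √(p(1−p)) at the true group shares. State the event proportion used, the length of follow-up it represents, and the sidedness of alpha.
2. If the group sizes are also revised (for intensification, only people who reach the HbA1c threshold; the cohort window from 2006/7 to 2018), recompute from the revised sizes. The figures in the verdict apply only to the sizes now printed.
3. Relabel the statin row as odds ratios, which agrees with the logistic regression specified for that outcome in section O. Put the two values in the same order in text and table, since the text lists 1.18 first and the table gives South Asians 1.15.
4. Replace β=0.90 in the table heading with power=0.90.
5. Rest the closing clinical-significance statement on the corrected table.

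The cost is a short recalculation and a table edit. Six figures become less favourable; no patient, outcome definition or analysis method changes.
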